## 2. Purpose

The purpose of the study is to investigate and describe how quickly subcutaneous infused fluid is absorbed, and is available to the circulation in acutely ill elderly patients compared to non-acutely ill elderly. By “acutely ill” is meant patients who have been admitted acutely and are currently being treated for an acute condition. By "not acutely ill" is meant patients who are not currently being treated for an acute illness, but may well have chronic diseases in a stable phase. Our hypothesis is that fluid is absorbed more slowly in the acutely ill than in the healthy. Subcutaneous fluid administration is used in elderly patients in need of parenteral fluid supplementation. Guidelines describe that it should only be used on stable patients . By determining the rate of absorption and how quickly the fluid is available to the circulation, the patient group in which subcutaneous fluid infusion is indicated can be clarified and possibly expanded. There has also been an increased focus on subcutaneous medication , and this study may increase awareness of the changes that occur in the elderly person's body during acute illness.

### Background:

The purpose of parenteral hydration is to supply fluid to the circulation. In intravenous hydration, this is achieved, but in subcutaneous hydration, the fluid must first be absorbed from the subcutaneous space to the circulation to achieve the desired effect.

To be able to relevantly evaluate the effect of subcutaneous hydration, we should know the rate of absorption. Lipschitz et al. examined in 1991 absorption rate and found that the liquid was available within an hour. However, their study was performed on healthy + 65-year-olds and with the addition of hyaluronidase (which increases the rate of absorption and is no longer used.) 

By subcutaneous infusion of a crystalloid solution, most of the fluid is absorbed through passive diffusion to the capillaries,  but in acute disease, the leakage from the capillaries increases.  The increased leak can potentially decrease the rate of absorption of the liquid, thereby prolonging the infusion time from the power in the circuit. Alternatively, the acute disease may decrease the resistance in the subcutaneous space and thus increase the absorption surface, thereby increasing the rate of absorption.

Radioactive markers can be used to assess both the rate of absorption from the subcutis (decrease in radioactivity in the subcutis) and the presence in the circulation (measurable radioactivity in blood samples). Lipschitz et al. used both pertechnetate ( $TcO_4^-$ ) and tritiated water and showed that pertechnetate had the same rate of absorption as tritiated water. 

### 3. Method

The trial is a case-control study with trial participants as their own controls. We will recruit geriatric patients currently hospitalized. We will invite patients back 8 weeks after discharge to investigate whether there is a difference between acutely ill and not acutely ill (stable phase). We expect that only some of the included patients want / can participate 8 weeks after discharge.

Patient flow:

1. Inpatient physicians assess whether some of the hospitalized patients are relevant to include.
2. Oral and written information is given to relevant patients while their relatives are present.
3. 24-48 hours reflection time.
4. Signing of consent form.
5. Patients participate in the first study (absorption during acute illness).

The examination (same for the first and second time):

6. 9:00: The patient arrives at the experimental room.

The content of the trial for the patient is reviewed again.

7. 9:15: Insertion of subcutaneous needle into abdominal skin and blood sampling needle into a large vein (v. Cubiti).
8. 9: 30-10: 30: Infusion of 250 ml NaCl with 30 MBq pertechnetate mixed in.
9. 9: 30-15: 00: Detection of gamma activity over the infusion site and in drawn blood.
10. 3-6 weeks after the patients have been discharged from the hospital, we contact them again for to find a date for another study.
11. The second study follows the same method as the first (points 6-9).

The subcutaneous needle is: "BD Saf-T-Intima™ GA22 - Integrated Safety Catheter System". Blood samples taken during the experiment will be taken by applying a heparinized venflon in the v. Cubiti.

### 4. Statistical considerations

Lipschitz et al. described in their technical article the rate of absorption by an absorption constant found by nonlinear regression. They found an absorption constant of  $2.29 \text{ h}^{-1}$  for subcutaneous infusion with hyaluronidase but do not describe values without hyaluronidase. If we assume a difference of 15% between acutely ill not acutely ill (we have no data to base this on, so this is an

estimate) and use 2.29 hours as non acutely ill value. We base the standard deviation from Lipschitz first infusion in each patient which was = 0.3 hour. With an alpha of 0.05 and a beta of 0.80, we get a group size of 6 (paired T-test).

As we expect that a large proportion of patients do not have the desire or energy to carry out the second examination, we expect to have to recruit approx. 15 participants.

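### The reference rate of 2.29 h⁻¹ was measured with hyaluronidase, so the planned difference of 0.34 h⁻¹ is probably too large; power falls with it if the SD stays at 0.3 h⁻¹

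*Protocol*

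**What the plan says.** Section 4 (Statistical considerations) takes its planning figures from an earlier study in elderly subjects. Its authors are said to give 2.29 h⁻¹ "for subcutaneous infusion with hyaluronidase but do not describe values without hyaluronidase". The protocol goes on to "use 2.29 hours -1 as non acutely ill value".

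The effect and SD are then set:

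- Effect: "If we assume a difference of 15% between acutely ill not acutely ill". The protocol says openly that no data support the 15%.
- SD: taken from the same study's "first infusion in each patient which was = 0.3 hour", an absolute value in h⁻¹.
- Result: "With an alpha of 0.05 and a beta of 0.80, we get a group size of 6 (paired T-test".
- Recruitment: because many are not expected to return for the second examination, "we expect to have to recruit approx. 15 participants".

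Two other places bear on the reference rate. The Background says the earlier study was done "with the addition of hyaluronidase (which increases the rate of absorption and is no longer used". Section 3 (Method) describes the procedure, the same at both visits, as "Infusion of 250 ml NaCl with 30 MBq pertechnetate mixed in".

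**The concern.** The three sections do not fit together. The Background says that hyaluronidase raises the absorption rate and has been abandoned. Section 3 lists none in the infusate. Section 4 nevertheless takes the hyaluronidase value as the rate expected in stable patients, and calculates 15% of that value as the difference to detect.

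On the protocol's own reasoning, the stable-phase rate in this trial should be below 2.29 h⁻¹, and 15% of a smaller rate is a smaller absolute difference. Section 4 sets that difference against an SD fixed in h⁻¹. If the SD does not fall with the rate, the standardised effect is smaller than planned. A null result could then be read as showing no slowing in acute illness when the trial had little chance of finding a 15% slowing. That matters because Section 2 (Purpose) hopes the result may clarify, and possibly widen, the group in whom subcutaneous infusion is indicated.

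**Working it through.** **Inputs from Section 4.** Reference rate k = 2.29 h⁻¹; relative difference 15%; SD 0.3 h⁻¹, used as the SD of the paired differences; alpha 0.05, taken as two-sided because sidedness is not stated; the beta of 0.80 read as power 0.80; paired t-test.

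**Step 1: the plan's own figure.**

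- Difference: δ = 0.15 × 2.29 = 0.3435 h⁻¹.
- Standardised effect: d = 0.3435 / 0.3 = 1.145.
- Normal approximation: n = [(1.960 + 0.842) / 1.145]² = 5.99, so 6 pairs. The stated figure reproduces.

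**Step 2: the same inputs with the exact paired t-test.** With 6 pairs there are 5 degrees of freedom, the critical value is 2.571 and the noncentrality is 1.145 × √6 = 2.80. Power is 62%. Reaching 80% takes 9 pairs (8 pairs give 79%, 9 give 85%). This gap between 80% and 62% comes from the approximation and has nothing to do with hyaluronidase. The effect of the reference rate has to be counted from 62%.

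**Step 3: a lower reference rate with the SD fixed at 0.3 h⁻¹.** The document gives no rate without hyaluronidase, so the rates below 2.29 are assumptions that show a range. d = 0.15 × k / 0.3.

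| k (h⁻¹) | δ (h⁻¹) | d | Power, 6 pairs | Pairs for 80% |
|---|---|---|---|---|
| 2.29 (protocol) | 0.3435 | 1.145 | 62% | 9 |
| 2.0 (assumed) | 0.300 | 1.00 | 51% | 10 |
| 1.5 (assumed) | 0.225 | 0.75 | 32% | 16 |
| 1.0 (assumed) | 0.150 | 0.50 | 17% | 34 |

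**Step 4: a lower reference rate with the SD proportional to it.** CV = 0.3 / 2.29 = 13.1%. Then d = 0.15k / [k × (0.3 / 2.29)] = 0.15 × 2.29 / 0.3 = 1.145 for every k. Power with 6 pairs stays at 62%, and 9 pairs are still needed for 80%.

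**Step 5: the difference 6 pairs can detect at SD 0.3.** Exact 80% power with 6 pairs needs d = 1.435, so δ = 1.435 × 0.3 = 0.43 h⁻¹. That is 0.43 / 2.29 = 19% of 2.29, 0.43 / 1.5 = 29% of 1.5, or 0.43 / 1.0 = 43% of 1.0.

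**Step 6: if all 15 recruits completed both visits.** With the SD at 0.3, power for a 15% difference would be 98% at 2.29, 95% at 2.0, 77% at 1.5 and 44% at 1.0. It drops below 80% once the reference rate is under about 1.56 h⁻¹.

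**The case against.** The strongest answer is that the protocol hides nothing. It says that 2.29 was obtained with hyaluronidase, that its source gives no value without it, and that the 15% is a guess. It used the only figure it had. This stands in part: the input is disclosed, so the fault lies in not carrying its known direction into the calculation or showing a range.

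The second answer concerns power. A reader might infer that power is overestimated because of hyaluronidase. The documents support that direction for the rate and for the absolute difference, but not for power. The effect is defined as a percentage and the SD comes from the same earlier study. If the SD shrinks with the rate, the loss of power is nil (step 4). This stands, and the loss must be stated as conditional. It does not clear Section 4, which enters the SD in absolute units and does not say whether it is expected to carry over.

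A reader might also compare 51%, 32% or 17% with the stated 80% and put the whole gap down to hyaluronidase. That is wrong, because the part from 80% to 62% comes from the normal approximation. Nor does the protocol show that a 15% slowing would be almost undetectable. That needs an assumed rate near 1.0 h⁻¹, an unchanged SD and only 6 completers. Six is the calculated requirement and not a cap, and about 15 are to be recruited. Those 15 are justified only by expected non-return, however, so they were not planned as a margin for an optimistic rate.

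**Conclusion.** The point holds as an unadjusted planning input. The reference rate was measured under conditions that the protocol itself says raise absorption and are no longer used. The planned difference of 0.34 h⁻¹ is therefore probably too large, by an amount that the document does not allow one to calculate.

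The consequence for power depends on an assumption that Section 4 does not state. With the SD fixed at 0.3 h⁻¹, power with 6 pairs falls from 62% to between 51% and 17% over assumed rates of 2.0 to 1.0 h⁻¹. With a constant CV of 13% it stays at 62%. In neither case do 6 pairs give 80% in the exact two-sided paired t-test.

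These figures assume a two-sided test, and that 0.3 h⁻¹ is the SD of the within-patient differences. The protocol describes it as coming from each patient's first infusion, so it looks like a between-patient SD. The two are equal only when the correlation between a patient's two visits is 0.5. That hyaluronidase is not used here is inferred from the Background and from the infusate described in Section 3.

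**What to change.** Change Section 4 as follows:

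1. State whether the SD is taken as fixed in h⁻¹ or as proportional to the rate.
2. Express the 15% effect as a ratio of the acute-phase to the stable-phase constant, on the log scale, and plan on the CV of the paired ratio.
3. Replace the single claim of 6 pairs for 80% power with exact paired-t power, or the detectable percentage difference, over reference rates at or below 2.29 h⁻¹. The percentages in step 5 show the form for a fixed SD.

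The first-visit infusions should not be used to supply the missing inputs. They are acute-phase measurements, so they do not give the stable-phase rate. Their spread is between patients, so they do not give the SD of the paired differences either.

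The cost is some rewording, a short recalculation and a less favourable stated power. The restatement itself needs no extra patients or procedures. It does not add power; it states correctly what the planned number of pairs can show.

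### The paired t-test is sized with an SD across patients used as the SD of within-patient differences, so the 80% power for 6 pairs rests on an unstated correlation and could be too high or too low

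*Protocol*

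**What the plan says.** Protocol section 3 (Method) describes a within-patient comparison: "The trial is a case-control study with trial participants as their own controls". Each patient is examined during the acute admission, and those able to return are examined again 8 weeks after discharge.

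Protocol section 4 (Statistical considerations) gives these inputs:

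- An absorption constant of 2.29 per hour is used "as non acutely ill value".
- The effect is an admitted guess: "If we assume a difference of 15% between acutely ill not acutely ill".
- The SD is taken from the earlier study's "first infusion in each patient which was = 0.3 hour"⁻¹.
- The result is given as "With an alpha of 0.05 and a beta of 0.80, we get a group size of 6 (paired T-test").

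To allow for patients who do not return, the section adds: "we expect to have to recruit approx. 15 participants".

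The protocol gives no SD of the within-patient difference, no correlation between the two visits, and no conversion from one to the other.

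**The concern.** An SD computed from one infusion per patient measures how much patients differ from one another. A paired t-test removes the part of that spread that is stable within a patient. What remains is the SD of the acute-minus-stable difference, and the two SDs coincide only for one particular correlation between visits. If the first is entered where the second belongs, the stated power depends on a correlation that nobody has chosen or defended.

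The stated sample size is the figure at stake. Participants have no health benefit from taking part and receive a radiation dose at each visit, which section 14 justifies by scientific value. How likely 6 pairs are to show the assumed difference bears on that justification, and the protocol offers one unqualified power figure for it.

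**Working it through.** **Inputs from protocol section 4.** Reference value 2.29 per hour; difference 15%; SD 0.3 per hour; alpha 0.05; power 80% (written as a beta of 0.80 and read here as power); paired t-test. Sidedness is not stated, so two-sided is used first.

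**Step 1: the difference.** 0.15 × 2.29 = 0.3435 per hour.

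**Step 2: reproduce the stated 6.** The paired normal formula is n = (SD_diff × (z₀.₉₇₅ + z₀.₈₀) / difference)². With SD_diff = 0.3:

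n = (0.3 × (1.960 + 0.842) / 0.3435)² = 5.99, so 6 pairs.

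This is the stated figure. Other variants with 0.3 do not give it:

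| Variant | n for 80% power |
|---|---|
| Normal, paired, two-sided | 6 |
| Normal, paired, one-sided | 5 |
| Exact t, paired, two-sided | 9 |
| Exact t, paired, one-sided | 7 |
| Normal, unpaired, two-sided | 12 per group |

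The protocol's 6 therefore comes from using 0.3 directly as the SD of differences.

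**Step 3: what that implies.** If both visits have SD 0.3 and correlation rho (equal SDs are my assumption), then

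SD_diff = 0.3 × √(2(1 − rho)).

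Setting SD_diff = 0.3 gives 2(1 − rho) = 1, so rho = 0.5.

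**Step 4: power with 6 pairs as rho varies.** The normal column is Φ(0.3435 × √6 / SD_diff − 1.96), on the same footing as the protocol's own figure. The exact column uses the noncentral t distribution with 5 degrees of freedom.

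| rho | SD_diff | Power, 6 pairs, normal | Power, 6 pairs, exact two-sided t | Pairs for 80%, exact t |
|---|---|---|---|---|
| 0 | 0.424 | 51% | 36% | 15 |
| 0.25 | 0.367 | 63% | 46% | 12 |
| 0.5 | 0.300 | 80% | 62% | 9 |
| 0.75 | 0.212 | 98% | 88% | 6 |

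Each power column, read downwards, shows the effect of the correlation, which is the present point. The gap between the two columns in a row, such as 80% against 62% at rho = 0.5, is a separate matter: the normal approximation is too optimistic for a t-test on 6 pairs.

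**Step 5: threshold.** By the exact two-sided t-test, 6 pairs give 80% power when SD_diff is at most about 0.239, which means rho of about 0.68 or more (1 − 0.2394² / (2 × 0.3²) = 0.68). If the test were one-sided, the threshold would be about 0.53, and 6 pairs would give 53%, 63% and 78% at rho 0, 0.25 and 0.5.

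**Step 6: dependence on equal SDs.** The value 0.5 changes if the acute visit is more or less variable. Keep the stable SD at 0.3 and take illustrative acute SDs. With 0.45, SD_diff = 0.3 needs rho = 0.45² / (2 × 0.3 × 0.45) = 0.75. With 0.20, it needs rho = 0.20² / (2 × 0.3 × 0.20) = 0.33.

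**The case against.** **The error need not be unfavourable.** This stands. Both visits involve the same person, an abdominal infusion site, the same needle type, the same volume and the same procedure, and such conditions favour a high correlation. Other features point the other way. Recovery lies between the visits, and the Background allows that acute illness may either slow or speed absorption; if patients respond in different directions, the SD of differences grows. The protocol does not settle which consideration prevails. A reader might infer that the trial is shown to be under-powered, but the documents do not support that, since 6 pairs suffice if rho is about 0.68 or more.

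**The fall from 80% to 62% is not due to the correlation.** This also stands. At rho = 0.5 that fall comes entirely from using the t distribution in place of the normal approximation, and it should not be charged to the choice of SD.

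**About 15 patients will be recruited.** This does not answer the point. Section 4 gives that number to allow for non-return around a target of 6 pairs. At rho = 0 all 15 would have to complete both visits to give 80% power, which the protocol does not expect.

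**Other inputs are equally soft.** This is true. The 15% is declared a guess, and the SD comes from infusions with hyaluronidase in healthy people over 65. That limits how much weight any sample size here can bear and argues against a stronger grading. But the protocol flags the effect size as an estimate and gives no such warning about the SD or the correlation.

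**The arithmetic is right.** It is, for the numbers entered. The fault lies in which SD was entered.

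**Conclusion.** The point holds as an unstated and unsupported assumption. By the protocol's own description, 0.3 per hour is an SD across patients, and the stated "we get a group size of 6 (paired T-test") is reproduced only by treating it as the SD of within-patient differences. With equal SDs at both visits, that amounts to a correlation of 0.5.

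On the protocol's own formula, power with 6 pairs runs from 51% at rho = 0 to 98% at rho = 0.75. By the exact two-sided t-test it runs from 36% to 88%. The unqualified 80% is therefore not supported by its inputs, although the true power may lie on either side of it.

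The conclusion rests on the protocol's wording about the first infusions (the cited source is not at hand), on reading the beta of 0.80 as power, on equal SDs at the two visits, and on two-sided testing. The range 0 to 0.75 for rho is illustrative, because the protocol gives no value. It should be corrected, but it does not invalidate the design.

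**What to change.** Restate the calculation in section 4 in one of two ways:

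- give an SD of the within-patient acute-minus-stable difference, with its source; or
- keep 0.3 as the SD at a single visit, and state the assumed correlation and the assumption of equal SDs at both visits.

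In either case, replace the single 80% for 6 pairs with exact-t power for 6 pairs over rho from 0 to 0.75 (36%, 46%, 62% and 88% at 0, 0.25, 0.5 and 0.75), and state whether the test is two-sided.

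The mention of a first infusion suggests that the source also had repeat infusions, though this cannot be checked here. If a repeatability (within-patient) SD is available from them, multiply it by √2 before using it as an SD of differences. Treat the result as optimistic, because it leaves out how patients vary in their response to acute illness.

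The cost is one recalculation and a few reworded sentences. The drawback is that the stated power becomes a range that may look less favourable. The fix does not itself require a change to recruitment. If the sponsor chose to aim for more pairs, the protocol's implied completion rate (6 of 15, or 40%) would mean about 23 recruits for 9 pairs (9 / 0.4 = 22.5) and about 38 for 15 pairs (15 / 0.4 = 37.5).

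### The planned 6 pairs come from a normal approximation; the paired t-test that the protocol names has about 62% power with 6 pairs, not 80%

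*Protocol*

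**What the plan says.** Protocol Section 4 (Statistical considerations) contains the only sample-size justification. It takes 2.29 per hour from a published study as the value when not acutely ill, assumes a 15% difference between the two states, and takes an SD of 0.3 per hour from the first infusion in each patient of that study. It then states: "With an alpha of 0.05 and a beta of 0.80, we get a group size of 6 (paired T-test". Because many patients are not expected to come back for the second examination, it adds that "we expect to have to recruit approx. 15 participants".

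The section does not say whether the test is one- or two-sided, and gives neither the SD of the within-patient differences nor a within-patient correlation. On direction, Section 2 (Purpose) says "Our hypothesis is that fluid is absorbed more slowly in the acutely ill than in the healthy", while the Background in the same section also allows the opposite: "the acute disease may decrease the resistance in the subcutaneous space and thus increase the absorption surface".

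**The concern.** Six pairs is a very small sample for a t-test. With 5 degrees of freedom the SD is poorly estimated, and the critical value is well above the normal one. A formula that ignores this can mislead by a few pairs, and at this size a few pairs matter a great deal. The stated 6 looked like the output of such a formula, although the text attributes it to a paired t-test.

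If so, a study that ends with the planned number of pairs has nearly twice the stated risk of missing the difference it was designed to find. A non-significant result would then be read as coming from a study with 80% power. The recruitment figure of about 15 is presented as cover for non-return around the same 6.

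The same sentence calls 0.80 beta. Read literally, that is 20% power.

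**Working it through.** **Inputs, all from Section 4**
- Difference: 0.15 × 2.29 = 0.3435 per hour.
- SD: 0.3 per hour, used directly as the SD of the paired differences.
- Standardised difference: d = 0.3435 / 0.3 = 1.145.
- Alpha 0.05; power 0.80 (reading the stated beta as power).

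**Step 1: reproduce the protocol's 6.** Two-sided normal formula:

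n = (z₀.₉₇₅ + z₀.₈₀)² / d² = (1.960 + 0.842)² / 1.145² = 7.849 / 1.311 = 5.99, rounded up to 6.

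Under this approximation, power with 6 pairs is 80.1%. The one-sided normal formula gives 4.72, rounded up to 5. A two-sample normal formula gives 12 per group (two-sided) or 10 (one-sided). Of these, only the two-sided paired normal formula returns 6.

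**Step 2: power of the test actually named.** A paired t-test on n pairs has n − 1 degrees of freedom. Its power comes from the noncentral t distribution with noncentrality d√n. With 6 pairs the noncentrality is 1.145 × √6 = 2.80 and the two-sided critical value is 2.571.

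| Completed pairs | Two-sided power | One-sided power |
|---|---|---|
| 6 | 61.6% | 77.6% |
| 7 | 71.5% | 84.7% |
| 8 | 79.3% | 89.6% |
| 9 | 85.2% | 93.1% |

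At least 80% power needs 9 pairs two-sided, or 7 one-sided.

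**Step 3: what 6 pairs can detect.** Two-sided 80% power with 6 pairs needs d = 1.435. That is 1.435 × 0.3 = 0.43 per hour, or 0.43 / 2.29 = 18.8%, against the assumed 15%.

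**Step 4: dependence on the meaning of 0.3.** If 0.3 is a between-patient SD, the SD of the differences is 0.3 × √(2(1 − ρ)), where ρ is the within-patient correlation. The protocol gives no ρ, so a range is shown (two-sided, exact):

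| ρ | SD of differences | Power with 6 pairs | Pairs for 80% |
|---|---|---|---|
| 0 | 0.424 | 36% | 15 |
| 0.25 | 0.367 | 46% | 12 |
| 0.5 | 0.300 | 62% | 9 |
| 0.6 | 0.268 | 71% | 7 |
| 0.7 | 0.232 | 82% | 6 |

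Power with 6 pairs reaches 80% at ρ of about 0.68. At that correlation the normal formula gives 3.8, rounded up to 4, so this is not how 6 was obtained.

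**Step 5: recruitment.** Six pairs from 15 recruits implies a return rate of 6/15 = 40%. Nine pairs from 15 needs 9/15 = 60%. At 40% return, nine pairs would need 9/0.40 = 22.5, so about 23 recruits.

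**The label.** A literal beta of 0.80 would need only 3 pairs on these inputs (power 21.6%). The stated 6 is therefore consistent with 0.80 meant as power.

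**The case against.** The arithmetic is not in dispute; the objections concern how firmly 62% can be stated and how much it matters.

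- **Sidedness is not stated, and the hypothesis is directional.** On a one-sided reading the gap is small: 77.6% against 80%, or one pair. The SD is also given to one figure only; an unrounded 0.28 would give 82.3% one-sided with 6 pairs. It stands that the protocol's text does not compel a two-sided test. But two-sided is the usual default, the Background allows an effect in either direction, and the 6 itself comes from a two-sided calculation. Rounding does not rescue a two-sided test: even with an SD of 0.25, 6 pairs give 76.7% and 7 are needed.
- **0.3 looks like a between-patient SD.** This stands as a gap in the plan, but it works in both directions. A correlation of about 0.68 or more would make 6 sufficient, and nothing in the protocol supports one. Below 0.5 the shortfall is worse, and 9 pairs would also be too few.
- **About 15 will be recruited.** If 9 or more return, power is at least 85% and nothing is lost. No return rate is stated, so the 40% is inferred by division. Still, 15 is offered as cover for non-return, not as extra power.
- **The 15% is an admitted guess, and 2.29 was obtained with hyaluronidase.** True power is therefore uncertain whatever is calculated. That does not excuse a result that fails to follow from its own inputs.
- **The beta label is an obvious slip.** Agreed; it matters only because it sits in the sentence that needs correcting.

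**Conclusion.** The concern holds. The stated 6 does not follow from the protocol's inputs and the test it names. With a two-sided alpha of 0.05 and 0.3 as the SD of the paired differences, 6 pairs give 61.6% power and 9 are needed. The chance of missing the assumed 15% difference with 6 completed pairs is about 38%, not 20%.

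The 62% rests on those two readings. Together they are the reading of the stated inputs that yields 6, and a one-sided t-test at the stated SD also falls short of 80%. The error is in the only sample-size justification and should be corrected.

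**What to change.** Rewrite the sample-size paragraph in Section 4:

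1. State the sidedness, and replace beta 0.80 by power 0.80 (beta 0.20).
2. State the SD of the within-patient differences, or the between-patient SD with an assumed correlation, and recompute from that.
3. If 0.3 is confirmed as the SD of the differences and the test is two-sided, either plan for 9 completed pairs, or keep 6 and say that power is about 62% and that the difference detectable with 80% power is about 19%.
4. Express the target as completed pairs, and give the assumed return rate behind the recruitment figure.

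Keeping 6 costs one paragraph and a less favourable stated power, with no extra enrolment. Choosing 9 leaves recruitment at 15 if 60% return, and raises it to about 23 if only 40% do.
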